## Abstract

**Background:**

Distal upper limb pain (pain affecting the elbow, forearm, wrist, or hand) can be non-specific, or can arise from specific musculoskeletal disorders. It is clinically important and costly, the best approach to clinical management is unclear. Physiotherapy is the standard treatment and, while awaiting treatment, advice is often given to rest and avoid strenuous activities, but there is no evidence base to support these strategies. This paper describes the protocol of a randomised controlled trial to determine, among patients awaiting physiotherapy for distal arm pain, (a) whether advice to remain active and maintain usual activities results in a long-term reduction in arm pain and disability, compared with advice to rest; and (b) whether immediate physiotherapy results in a long-term reduction in arm pain and disability, compared with physiotherapy delivered after a seven week waiting list period.

**Methods/Design:**

Between January 2012 and January 2014, new referrals to 14 out-patient physiotherapy departments were screened for potential eligibility. Eligible and consenting patients were randomly allocated to one of the following three groups in equal numbers: 1) advice to remain active, 2) advice to rest, 3) immediate physiotherapy. Patients were and followed up at 6, 13, and 26 weeks post-randomisation by self-complete postal questionnaire and, at six weeks, patients who had not received physiotherapy were offered it at this time. The primary outcome is the proportion of patients free of disability at 26 weeks, as determined by the modified DASH (Disabilities of the Arm, Shoulder and Hand) questionnaire.

We hypothesise (a) that advice to maintain usual activities while awaiting physiotherapy will be superior than advice to rest the arm; and (b) that fast-track physiotherapy will be superior to normal (waiting list) physiotherapy. These hypotheses will be examined using an intention-to-treat analysis.

**Discussion:**

Results from this trial will contribute to the evidence base underpinning the clinical management of patients with distal upper limb pain, and in particular, will provide guidance on whether they should be advised to rest the arm or remain active within the limits imposed by their symptoms.

**Trial registration:**

Registered on http://www.controlled-trials.com (reference number: ISRCTN79085082).

## Background

Upper limb pain is common and responsible for considerable disability, demand for health care and lost productivity. Among working-aged respondents to a recent population survey in England, 15% had consulted a GP within the past year with upper limb pain [1]; 5% had seen a specialist; 14% reported symptoms persisting more than six months; and 10% reported disabling pain [2]. Further, data from the UK Labour Force Survey indicate that work-attributed cases of upper limb disorder cause an estimated annual loss of 4.7 million working days [3]. Upper limb pain is more likely to become persistent if accompanied by poor mental health, adverse psychosocial factors, including a somatising tendency (tendency to be distressed by common physical symptoms), and adverse beliefs concerning health and activity [4,5]. Indeed, it is plausible that response to treatment may vary importantly between subgroups defined by such characteristics.

Distal upper limb pain is defined as pain in the elbow, forearm, wrist or hand, may be non-specific in origin, or may arise from a number of specific disorders (e.g. medial and lateral epicondylitis, and tenosynovitis). In a study of patients presenting to primary care and physiotherapy services with upper limb pain, 42% of patients had pain in the distal arm and at twelve months 48% were still in pain, and 19% reported unremitting pain (never pain-free for as long as seven consecutive days) [5]. Although distal upper limb pain is clinically important, and costly, the best approach to managing symptoms is unclear.

### Evidence for the effectiveness of advice in the treatment of upper limb pain

Patients with upper limb pain are commonly referred to physiotherapy and, while awaiting treatment, are often advised to rest the arm and avoid purported harmful activities as a precautionary measure. Indeed, online health advice offered by the UK National Health Service (NHS) states that ‘it is likely that your GP will probably advise you to temporarily stop doing the task or activity that is causing your symptoms’ [6]. Similarly, many employers and occupational physicians are wary of allowing employees with distal upper limb pain to continue with forceful or repetitive work activities for fear of possible litigation. However, such advice lacks an evidence base. A search of MEDLINE and BIDS Embase in 2009 (at the time the funding application for the current trial was prepared) confirmed that no randomised controlled trial has hitherto investigated the benefits of resting the painful arm as compared with remaining active within the limits of pain. This omission is both important and surprising. An analogy can be drawn with non-specific low back pain, which shares many aetiological and prognostic factors and which for many years was managed by bed rest. However, trials – and, latterly, large-scale community health campaigns – have demonstrated that back pain prognosis is improved if patients are advised to remain active [7,8].

Written information providing evidence-based advice to patients with back pain (*The Back Book*) has been shown to be effective in promoting positive beliefs and contributing to improved clinical outcomes [9,10]. The way in which the advice is imparted is based firmly on a biopsychosocial approach: traditional beliefs about the relationship between activity and pain are challenged, the benefits of remaining active are contrasted with the disadvantages of undue rest, and individuals are empowered to take responsibility for their recovery. This differs conceptually from a biomedical approach in which the patient is a passive recipient who is told what has gone wrong (injury), how it is diagnosed, and what healthcare can do to fix it. The activity-promotion approach has been extended to the management of neck injury (*The Whiplash Book*), where a booklet focusing on reducing anxiety about the injury, and stressing the benefits of remaining active, has been well received by patients and caused a positive shift in beliefs [11]. More recently available is *The Arm Book* which also provides evidence based advice on how to deal with upper limb pain or injury. However, its effectiveness is currently unproven [12].

It seems plausible that patients with distal upper limb pain might benefit from a similar approach to back pain. Many such cases (like cases of back pain and whiplash injury) arise in the absence of well-defined local pathology, and the natural history and predictors of arm pain share much in common with these other musculoskeletal disorders – fear-avoidance, health anxiety, pessimistic attitudes, psychological distress and adverse psychosocial factors [4,5,13]. We hypothesise a number of possible mechanisms through which we may hasten improvement in function, by challenging disadvantageous beliefs about ‘injury', reducing fear and distress, and encouraging self-management and the maintenance of an active approach to recovery. Whether patients with distal upper limb pain benefit from keeping active, as back pain sufferers do, is logically the next research question to address and well-conducted trials are needed to resolve these issues.

### Hypothesis/aims

The primary aim of this study is to investigate whether, among patients awaiting physiotherapy for distal upper limb pain (pain in the elbow, forearm, wrist or hand), advice to remain active and maintain usual activities results in a long-term reduction in upper limb pain and disability, compared with advice to rest.

Potential participants will be identified from patients with distal upper limb pain referred to physiotherapy. However, whether physiotherapy itself is efficacious in the management of distal upper limb pain is not well established. Therefore, in the context of the proposed trial, a pragmatic opportunity exists to determine the value of early physiotherapy in comparison with treatment that is delayed until the usual waiting list time. Therefore, a secondary aim is to determine, among the same patient population, whether immediate (‘fast-track’) physiotherapy results in a long-term reduction in upper limb pain and disability, compared with physiotherapy delivered at the usual waiting list time – typically, after a period of approximately seven weeks.

## Methods/design

### Study design overview

This paper presents the protocol for a multi-centre, randomised, controlled trial. Potentially eligible patients with distal upper limb pain are identified from waiting lists in out-patient physiotherapy departments. Recruited patients undergo telephone screening in the first instance, followed by a pre-trial assessment by a research nurse, to confirm eligibility and collect baseline information. Eligible patients are randomised to one of three groups:

• Group 1 – advice to remain active while awaiting physiotherapy treatment;

• Group 2 – advice to rest the arm while awaiting physiotherapy treatment; or

• Group 3 – immediate physiotherapy.

All participants are followed up by postal questionnaire 6, 13 and 26 weeks post-randomisation to determine arm pain and function. In addition, at six weeks, participants from Groups 1 and 2 who indicate that they still require physiotherapy are offered immediate treatment. Thus, this treatment will be delivered at around seven weeks equating, approximately, to that on a ‘usual care’ waiting list.

### Ethical issues

Ethical approval has been obtained from the South Central – Hampshire A Research Ethics Committee (11/SC/0107). All participants are required to provide written informed consent at initial assessment. Patients are required to consent to complete the study questionnaire, undergo the brief examination and, if eligible, to be randomised into one of the treatment groups. Participants are not being made aware that there are two different types of advice to prevent compromise of the advice being given.

### Identification of potential participants

From January 2012 to January 2014, male and female patients aged 18 years or older were identified from out-patient physiotherapy services in fourteen UK trial sites (see Table 1). Eligibility was established by screening referral letters for physiotherapy and confirmed by questioning and physical examination carried out by trained research nurses during an initial assessment visit. Patients were potentially eligible if they were referred (or self-referred) to out-patient physiotherapy for treatment of distal upper limb pain/disability. However, patients were excluded if they met one, or more, of the following criteria: (a) aged <18 yrs at the time of screening; (b) the patient had received previous physiotherapy for distal upper limb pain within the past twelve months; (c) the disorder was of a type for which physiotherapy of the distal upper limb was not the primary treatment (e.g. pain referred from the neck/shoulder); (d) the pain was due to a fracture, systemic inflammatory disease, or cancer; (e) the patient has complex regional pain syndrome; (f) symptoms were due to a specific condition for which advice to remain active is contraindicated (e.g. florid tenosynovitis); (g) the appointment was classed as an emergency; and/or (h) the patient was embroiled in a legal dispute regarding their arm pain.

**Table 1 T1:** Trial recruitment sites

**Centre**	**First patient randomised**	**Last patient randomised**
Aberdeen	03-Feb-12	04-Feb-14
Southampton	20-Feb-12	29-Apr-13
Brighton	16-Mar-12	07-Feb-14
Sussex	17-Aug-12	27-Dec-13
Stockport	13-Sep-12	23-Jan-14
Newcastle	27-Nov-12	14-Jan-14
Southend	03-Dec-12	19-Nov-13
King’s college	01-Feb-13	28-Jan-14
Wigan	11-Feb-13	10-Feb-14
Huddersfield	14-Feb-13	23-Jan-14
Leicester	14-Mar-13	28-Nov-13
Birmingham	28-Mar-13	06-Jan-14
Bath	08-May-13	18-Feb-14
St Helens	16-May-13	08-Oct-13

### Initial assessment visit

Patients who attended the initial assessment were asked to self-complete a questionnaire which asked about demographic characteristics (age, sex, social class); employment circumstances (including occupational activities); symptom history (e.g. unilateral or bilateral symptoms, duration, disability) and all prior treatments to date. In addition, data were collected on general health, physical and mental well-being, fatigue, other symptoms (headache/abdominal pain/chronic widespread pain), somatic distress, health beliefs (especially fear avoidance) and smoking status.

Patients also underwent a standardised upper limb examination: the Southampton Examination Schedule for Upper Limb Disorders which includes inspection and palpation of the upper limbs, and clinical provocation tests (including Finkelstein’s test, Phalen’s test and Tinel’s test). The Schedule is based on a national Delphi consensus, has been validated in hospital out-patient and community settings, and has been applied in previous large-scale epidemiological studies [14,15].

Both questionnaire and examination assessed factors were considered as important prognostic markers, potential modifiers of treatment response, baseline measure of outcomes, or were important for randomisation and minimisation.

### Randomisation process and allocation concealment

Randomisation was conducted by the Robertson Centre for Biostatistics, a registered clinical trials unit at the University of Glasgow.

Patients were allocated to one of the three treatment groups using a mixed randomisation and minimisation algorithm to maintain treatment balance with respect to treatment centre, laterality (dominant, non-dominant, bilateral), a broad categorisation of diagnosis (elbow disorder, or wrist/hand disorder), and baseline arm function, as assessed using a modified DASH score (the primary outcome measure, with scores grouped as 0–5, 6–8, or 9–11). For each new patient, the minimisation variables were entered into a web-based data collection system, created by the trials unit; the system then allocated the patient to one of the three groups. One third of patients were allocated completely at random, whilst two-thirds were allocated according to the minimisation algorithm. Randomisation to the three groups, or entry to the minimisation procedure, was determined according to a pre-specified allocation schedule generated using the method of randomised permuted blocks of nine participants. This schedule was known only to a restricted group of staff at the trials unit. Within the minimisation algorithm, in the event of a tie between treatment groups (i.e. when allocation to more than one group would provide an equally low level of imbalance), treatment was allocated at random between the tied treatment groups.

### Blinding

Because of the nature of the interventions, it was not possible to blind study participants. However, to prevent ‘contamination’ it is important that participants were unaware of the differing advice given to others. Therefore, patients were informed that if they participated, they would be randomised to immediate physiotherapy or advice, without giving explicit details about the nature of the advice (or even the fact that there were two advice groups).

Participants randomised to receive immediate physiotherapy were fast-tracked to treatment which they received at the earliest opportunity. Additional physiotherapy staff were provided in all participating trial centres so initial physiotherapy assessment (independent of the trial screening examination) and first treatment would occur in a matter of days, rather than weeks. Whilst this trial is intended to be pragmatic in so far as it is reflective of usual physiotherapy practice, we undertook additional work to ensure the treatment programmes were compliant with both the Medical Research Council’s and the CONSORT organisation’s guidance on developing and reporting complex interventions. In the early phases of the study we documented and developed the intervention to ensure it represents best usual care. This involved a review of appropriate treatment guidelines and the literature to ascertain current best practice. It also included discussions with physiotherapists involved in the trial in order to establish current practice and, if any differences were encountered, to reconcile the findings of the literature with actual clinical practice. A broad set of guidelines was developed in accordance with best practice which gave therapists the flexibility to treat patients on an individual basis without being overly prescriptive.

Further, it is important that the interventions be documented so they can be reported and replicated, and the physiotherapists who deliver the intervention be involved in this process (to facilitate compliance with the treatment protocol). Treatments were recorded using a standardised pro forma and record, for example, treatment modality, number and timing of appointments attended, and time to discharge.

### Follow-up and trial outcomes

Follow-up is still ongoing. Participants are followed up at 6, 13, and 26 weeks post-randomisation by self-complete postal questionnaires, and non-responders receive a reminder questionnaire after two weeks. After a further two weeks, non-responders are followed up by telephone, and are asked brief questions on the primary outcome only, using a standardised pro forma. In addition, at six weeks patients randomised to receive advice (Groups 1 or 2) receive a letter offering them a physiotherapy appointment which, if accepted, is received at the earliest opportunity. This approach, requiring an active opt-in to treatment, is consistent with current practice for patients not involved in the trial. Also, the delay between randomisation and the offer of appointment is equivalent to what would be usual care physiotherapy in most UK centres. Participants electing to receive physiotherapy are offered immediate treatment and receive that therapy, as per usual protocol (and as per Group 3), at the discretion of the treating physiotherapist. Although the precise treatment modalities given may differ between fast-track and delayed physiotherapy groups, this reflects usual care, where treatment choice may be dependent on time elapsed since initial referral and activities undertaken in the interim.

The DASH (Disabilities of the Arm, Shoulder and Hand) questionnaire is an instrument designed to measure physical function and symptoms in patients with single or multiple musculoskeletal disorders of the upper limb. It has been shown to have good test-retest reliability and validity. Further, it has high internal consistency, correlates well with other measures of arm function, and discriminates between persons who are/are not able to undertake activities of daily living, or work without restriction [17]. However, the DASH instrument has a number of important limitations in the context of the current trial. Specifically, (a) there is a lack of good quality reference data for the DASH from the United Kingdom; (b) the DASH instrument focuses on the whole of the upper limb and contains no items that are specific to the distal arm; (c) none of its elements relate explicitly to activity limited by pain; (d) the timeframe of inquiry (past seven days) is likely to limit study power for certain outcomes (e.g. difficulty changing a light-bulb) and is less relevant clinically in a trial designed to assess sustained recovery; and (e) some items are relevant only to subsets of the study population (e.g. preparing meals, making beds), rather than providing a question set based on activities that everyone is likely to perform.

Accordingly, we developed a modified instrument to determine arm function. Based in part and in format on the original DASH questionnaire, and called here the 'modified DASH', this instrument asks participants to rate difficulty in performing eleven pre-specified activities over the previous seven days because of pain in their distal upper limb (Figure 1). This modified DASH, which has improved face validity over the DASH for our purposes, has previously been used in a large population survey examining the outcome and prognostic determinants for upper limb pain presenting in primary care and to physiotherapy services [5]. In this pilot phase, the instrument was shown to be sensitive to change, and to track clinical recovery over the time interval of interest. It enables a well-powered, clinically relevant dichotomous outcome (full recovery versus not) to be studied.

**Figure 1 F1:**
[figure not shown]
Modified DASH.

Thus, for the current trial, the primary outcome is the proportion of patients free of disability at 26 weeks post-randomisation, as determined by the modified DASH. As a secondary outcome for participants randomised to Group 1/Group 2, we aim to determine the proportion who still seek physiotherapy at six weeks. In addition, we collect information on the type of treatments given, and time to discharge. Other secondary outcomes, in all participants, include: upper limb pain and function, coping, fear of movement, ability to function at work, aspects of general health and quality of life.

In addition, health care costs will be collected from participants using structured questionnaires. These will record distal upper limb related hospital admissions, out-patient attendances, and visits to/from relevant health professionals. Published UK sources of data on unit cost will be applied to value use of resources. For EQ-5D and SF-12 outcomes, published UK tariffs will be used to convert these data to quality of life weights.

### Statistical issues

#### Proposed sample size/power calculation

The study is powered to determine a difference in the proportion of patients fully recovered at 26 weeks post-randomisation, as assessed using the modified DASH. The principal analysis will consist of a comparison between participants in Group 1 and Group 2 (advice to maintain usual activities, versus advice to rest the arm). We have previously shown that, among persons with distal arm pain undergoing usual care, 51% were free of disability at six months, with little further improvement (up to 60%) at 12 months [5]. The trial is powered on the assumption that 70% of participants in Group 1 will be free of disability at six months. We require 148 subjects in each group in order to detect this difference with 90% power and an alpha of 5%. From previous trials with similar follow-up methods we anticipate, conservatively, that 80% of patients randomised will complete a follow-up questionnaire at 26 weeks [18]. Thus, we need to randomise 185 participants per group. We intend, in addition, to recruit 185 participants into Group 3 (immediate physiotherapy). Thus, we aimed to randomise 555 participants in total.

#### Statistical analysis

Analysis will determine whether, at 26 weeks post-randomisation, patients in Group 1 (advice to remain active and maintain usual participation) experience an improvement in upper limb pain and function, compared with those in Group 2 (advice to rest the painful arm). In addition, we will examine whether, at 26 weeks post-randomisation, patients who received immediate physiotherapy (Group 3) experience an improvement in upper limb pain and function compared with those who received delayed treatment (from Groups 1 and 2 combined).

Estimation of the treatment effects will be based on intention-to-treat and will be conducted at the end of the follow-up period (26 weeks after the final randomisation). To address the primary research question a logistic regression model will be fitted to estimate the odds ratio for full recovery at 26 weeks post-randomisation between Group 1 and Group 2. The model will include treatment group (as a three-level categorical variable), age (as a continuous variable, or categorical, depending on the nature of any association), and as categorical variables: sex, study centre, pain location (elbow, wrist/hand, or both), laterality (dominant, non-dominant, or bilateral) and baseline modified DASH score (0–5, 6–8, or 9–11). If small numbers in any of these sub-groups causes problems for model convergence, alternative specifications will be considered.

For the primary analysis of the impact of advice to remain active compared to advice to rest, the method of recycled predictions (using 1000 bootstrap samples) will be used to estimate the absolute difference in the probability of being fully recovered between the two groups, with a 95% confidence interval.

Likewise, for the secondary research question, the impact of early compared to delayed physiotherapy, the method of recycled predictions (using 1000 bootstrap samples) will be used to estimate the absolute difference in the probability of being fully recovered between the early physiotherapy group and the two delayed physiotherapy groups combined, with a 95% confidence interval.

Although the main analysis will classify the modified DASH score dichotomously – i.e. fully recovered (zero disabilities) or not – as a secondary analysis the modified DASH score will be considered as a continuous variable. A linear regression model will be fitted, including the treatment group, age, sex, study centre, pain location, laterality and baseline modified DASH score (as a continuous variable). Again, if small numbers in any of these sub-groups causes problems for model convergence, alternative specifications will be considered. To assess the impact of advice to remain active compared with advice to rest, and to compare early with usual care physiotherapy, appropriate contrasts will be applied to the coefficients of the above model to estimate the adjusted mean differences in modified DASH scores between Groups 1 and 2, and between Group 3 and the mean of Groups 1 and 2 combined, with 95% confidence intervals.

The above analysis will be repeated using the same outcome measures collected at different assessment time points (6 and 13 weeks post-randomisation). In addition, evidence of treatment effect heterogeneity will be assessed by including terms for interactions between treatment and each of the other variables in the regression models.

Finally, a cost-utility analysis will be performed to assess the health care and patient costs, and quality of life effects, associated with provision of each of the three treatments. A series of incremental cost per Quality Adjusted Life Year (QALY) ratios will be calculated. Sensitivity analysis will be employed to quantify the uncertainty surrounding the calculated ratios. In addition, non-parametric methods will be used for calculating the confidence intervals around cost per QALY ratios, using bootstrapped estimates of the mean cost and QALY differences. To summarise cost-effectiveness, cost effectiveness acceptability curves will be employed to show the probability that different interventions are cost effective for different values of willingness to pay per additional QALY.

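### The primary logistic model adjusts for baseline modified DASH only in the three minimisation bands; using the full 0–11 score would gain a little precision at almost no cost

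*Protocol article*

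**What the plan says.** All references are to the protocol article.

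- **Primary model** (Statistical analysis): a logistic regression for full recovery at 26 weeks. Its categorical covariates include "and baseline modified DASH score (0–5, 6–8, or 9–11". Alternative specifications are foreseen only if small subgroups cause convergence problems.
- **Allocation** (Randomisation process and allocation concealment): baseline function is a minimisation factor, "with scores grouped as 0–5, 6–8, or 9–11". The model bands are therefore the allocation bands.
- **Secondary model** (Statistical analysis): the linear regression of the modified DASH score uses "baseline modified DASH score (as a continuous variable".
- **Instrument and endpoint**: patients "rate difficulty in performing eleven pre-specified activities over the previous seven days" (Follow-up and trial outcomes). The primary analysis classes them as "fully recovered (zero disabilities) or not" (Statistical analysis). Eleven items and a top band ending at 11 imply a 0–11 score.
- **Entry** (Identification of potential participants): "Patients were potentially eligible if they were referred (or self-referred) to out-patient physiotherapy for treatment of distal upper limb pain/disability". None of exclusions (a) to (h) is a minimum score.

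**The concern.** The endpoint is a score of zero on the same instrument that is measured at baseline, so the baseline score is likely to be one of the strongest predictors of outcome. The lowest band covers six of the twelve possible scores. Within it, the model treats a patient with no or one limited activity as having the same expected outcome as a patient with five. Grouping is needed to run a minimisation algorithm, but a regression model has no such need, and the secondary model shows that the finer score can be used. Minimisation balances the bands and not the scores within them, so only the full score can adjust for chance differences within a band.

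What is at stake is the width of the confidence interval for the primary comparison, not its validity.

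**Working it through.** **1. The plan's own sample size.** Inputs from Proposed sample size/power calculation: "51% were free of disability at six months" under usual care, "70% of participants in Group 1 will be free of disability at six months", 90% power, alpha 5% (taken as two-sided) and 80% completion.

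- Mean proportion = (0.51 + 0.70)/2 = 0.605; difference = 0.19.
- n = [1.960·√(2·0.605·0.395) + 1.2816·√(0.51·0.49 + 0.70·0.30)]² / 0.19² = (1.355 + 0.869)² / 0.0361 = 137.0, so 138.
- With continuity correction: n = (137.0/4)·[1 + √(1 + 4/(137.0·0.19))]² = 147.4, so **148**, as stated.
- 148/0.80 = 185 per group, and 3 × 185 = 555, as stated.

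This calculation takes no credit for covariate adjustment. Uncorrected power at 148 per group is 92.1%. The form of the baseline covariate therefore cannot invalidate it.

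**2. How much of the score the bands keep.** For a uniform score on 0–11 (an assumption), total variance = (12² − 1)/12 = 11.92. The band means are 2.5, 7 and 10, with weights 0.50, 0.25 and 0.25 around 5.5. Between-band variance = 0.5·3² + 0.25·1.5² + 0.25·4.5² = 10.125, and 10.125/11.92 = 0.85. Across the other assumed distributions the share ranged from 0.69 to 0.85.

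**3. Effect on the primary comparison.** The article gives neither the baseline distribution nor its prognostic strength, so both were varied: four distributions (uniform, mid-weighted, low-weighted, high-weighted), with the odds of recovery falling by a factor of 1.1, 1.2, 1.35 or 1.6 per point. Each scenario had 2,000 simulated trials with 148 per arm, recovery fixed at 51% versus 70%, and the standardised risk difference (recycled predictions) as the estimate. Two further scenarios placed 5% or 10% of patients at score 0 and multiplied their recovery odds by a further e¹. Only Groups 1 and 2 and the baseline score were modelled; minimisation and the other covariates were left out.

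Selected results (ratios use unrounded standard errors):

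| Assumed baseline | Odds factor per point | SE, bands | SE, linear | Variance ratio | Power, bands → linear |
|---|---|---|---|---|---|
| High-weighted (17% at 0–5) | 1.10 | 0.0553 | 0.0553 | 0.999 | 92.7% → 92.7% |
| High-weighted | 1.20 | 0.0548 | 0.0546 | 0.995 | 93.4% → 93.6% |
| High-weighted | 1.35 | 0.0536 | 0.0533 | 0.987 | 92.4% → 92.5% |
| Low-weighted (69% at 0–5) | 1.35 | 0.0533 | 0.0525 | 0.970 | 93.7% → 94.4% |
| High-weighted | 1.60 | 0.0515 | 0.0509 | 0.974 | 94.8% → 95.1% |
| Mid-weighted | 1.60 | 0.0501 | 0.0492 | 0.966 | 96.5% → 96.7% |
| Uniform | 1.60 | 0.0461 | 0.0451 | 0.958 | 98.5% → 98.9% |
| Low-weighted | 1.60 | 0.0509 | 0.0493 | 0.937 | 95.8% → 97.0% |
| Low-weighted, 5% at score 0, jump at 0 | 1.20 | 0.0546 | 0.0540 | 0.980 | 94.5% → 94.7% |
| Low-weighted, 10% at score 0, jump at 0 | 1.20 | 0.0544 | 0.0536 | 0.971 | 92.9% → 93.8% |

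Over all scenarios with factors 1.1 to 1.35, the variance reduction was 0.1% to 3.0%; at 1.6 it was 2.6% to 6.3%.

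**4. In practical units.** A variance ratio of 0.970 is worth 1/0.970 − 1 = 3.1% more patients, about 9 of 296 completers. A ratio of 0.937 is worth 6.7%, about 20 of 296. In that most extreme case the 95% half-width falls from 1.96 × 0.0509 = 10.0 to 1.96 × 0.0493 = 9.7 percentage points.

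**5. What the bands already achieve.** In the low-weighted scenario at 1.35, bands against no baseline adjustment gave a variance ratio of 0.921; linear against none gives 0.921 × 0.970 = 0.893. The bands thus deliver 7.9 of 10.7 percentage points, about three quarters of the available gain.

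**The case against.** The strongest reply is that the bands are not arbitrary. They are the minimisation strata, and adjusting for an allocation factor in the form in which it was used is a recognised convention. The bands also avoid assuming that the log odds are linear in the score. Both points stand. They explain the choice and make it defensible, but they do not require it: the continuous score carries nearly all the information in the bands, and a spline fixed in advance removes the reliance on linearity.

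It can also be said that the secondary analysis already uses the continuous baseline. It does, but for a different outcome scale and a linear model, so it adds nothing to the precision of the primary odds ratio or risk difference.

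Three stronger readings are tempting, and the article supports none of them.

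- **That banding biases the result or leaves the trial underpowered.** Allocation is random, and chance imbalance within bands is already reflected in the confidence interval. The sample size reproduces without any credit for adjustment.
- **That the lowest band mixes patients who already meet the endpoint with those who have five disabilities.** The design permits this, since no minimum score is set, but nothing shows that anyone scored 0 at entry.
- **That a continuous covariate would solve the problem of such patients.** It would not. They would still count as recovered if they stayed at 0. That is a question of eligibility or endpoint, separate from how the covariate is coded.

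**Conclusion.** The point holds as a minor and inexpensive improvement, not as an error. The primary model discards baseline detail that is collected and is used elsewhere in the same plan. The cost is about 0–3% of the variance of the risk difference if the score is moderately prognostic, up to about 6% if it is strongly so, and about 1 power point at most (1.2 in the most extreme scenario). The direction was the same in every scenario shown, but the size rests wholly on assumed baseline distributions and slopes and on a simulation without minimisation or the other covariates. Validity, freedom from bias and the planned 148 per group are untouched.

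**What to change.** Before analysis, prespecify baseline modified DASH as a continuous 0–11 score in the primary logistic model, either linear or as a spline with knots fixed in advance. Keep the model with the three minimisation bands as a sensitivity analysis. The article reports that follow-up was still ongoing and that treatment effects are estimated only after it ends, so the change could be fixed in time.

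The cost is one line of specification, with no new data and no patients lost. The downside is small: a linear term assumes a functional form, and a spline spends one or two more parameters than a linear term (the bands themselves use two). The odds ratios from the two models should be expected to differ slightly, because a conditional odds ratio changes with the covariates. In the low-weighted scenario at 1.35 the mean log odds ratio was 0.898 with bands and 0.924 with the linear term, while the risk difference was 0.191 in both. Such a difference is no sign of instability.

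Optionally, add a sensitivity analysis that excludes any patients with a baseline score of 0. That criterion is fixed before randomisation, so the randomised comparison is preserved. If no one scored 0, the analysis falls away.
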